### Statistical analysis

Baseline characteristics of participants (age, number of cigarettes smoked per day, history of packed-years and number of previous cessation attempts) in all the three arms will be expressed as mean values ± standard deviation (SD). The null hypothesis will be adopted in comparing the outcomes (PAR, CAR, CO levels, MNWS score and SCL scores) between Arm 1 and Arm 3, Arm 2 and Arm 3, and finally between Arm 1 and Arm 2. In view of the small sample size for each arm, the Mann-Whitney-Wilcoxon two-sample rank sum test will be used for each Arm pair. Medians will be calculated with the quartiles and the Mann-Whitney *U*. Where possible, treatment effect for each Arm pair comparison will be expressed using the Hodges-Lehmann estimator with the 95% confidence intervals and significance levels.

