### Sample size calculation and randomisation

A convenience sample size of a total of 60 participants will be recruited, with 20 participants per arm after randomisation. Compared to other pilot studies, this sample size is deemed sufficient and appropriate statistical methods will be adopted to accommodate for foreseeable limitations during final analysis (see section on statistical analysis). Randomisation and allocation of subjects will be performed according to the CONSORT standards in terms of randomisation type[37], randomisation generation[38], allocation concealment[39]. All participants will be informed that they will be randomly allocated to one of the three study arms using a computer generated sequence created by the SPSS 11.0 (IBM^© ^SPSS^© ^Statistics, NY, USA). The random allocation will only be disclosed on the date of treatment commencement. Apart from Arm 3 (passive controls with no acupressure), blinding will be ensured in participants of Arm 1 (true acupuncture points) and Arm 2 (sham points). In particular, participants receiving acupressure will be told that the actual points chosen may vary over time to eliminate guessing amongst them during the study. Efforts will also be made to avoid contacts between all participants.

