### Baseline evaluation

Once eligibility is confirmed, all participants will undergo a pre-treatment baseline evaluation during week 1 (run-in period). All subjects will be subjected to a brief physical examination recording the weight, height, body-mass-index (BMI), waist circumference, resting blood pressure, resting heart rate and end-expiratory carbon monoxide level (CO) through the use of a hand-held Smoklyzer^©^. In addition, a brief history will be taken regarding their past and present health. Their smoking profile will also be assessed in terms of number of cigarettes smoked per day, smoking history in terms of pack-years, number of previous attempts of smoking cessation and methods used, and finally, their level of motivation to quit on Likert scale of 0-7.

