### Outcome measures

The primary outcome measures in our study will be 7-day point prevalent abstinence rate (PAR), continuous abstinence rate (CAR), end-expiratory carbon monoxide levels (CO), nicotine withdrawal symptoms according to the Minnesota Nicotine Withdrawal Scale (MNWS) and stress level according to the Stress Check List (SCL). PAR is defined as abstinence from tobacco smoking for the previous 7 days, whereas CAR is defined as abstinence since the target quit date. The time taken (T) to reach the quit date is also recorded. During the active intervention period (week 2 to week 7), the following will be assessed weekly: number of cigarettes smokes per day, CO, MNWS and SCL. At week 3, 5 and 7, CAR and PAR will be assessed. At week 13 and week 26, successful quitters will be assessed for CO, PAR, SCL and MNWS. At week 2 and week 8/one week after successful quitting, expectancy of treatment will be assessed in all participants with a modified 4-item Borkovec and Nau self-assessment credibility scale as adopted by Tough *et al. *[40] in acupuncture related studies.

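### CO, MNWS and SCL are compared without baseline adjustment, and the text lists no pre-treatment MNWS or SCL: a loss of precision, probably small for CO, but not a bias

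*Protocol article*

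**What the plan says.** The Statistical analysis section of the Protocol article covers "comparing the outcomes (PAR, CAR, CO levels, MNWS score and SCL scores) between Arm 1 and Arm 3, Arm 2 and Arm 3", and then Arm 1 against Arm 2. The test is fixed for all of them: "In view of the small sample size for each arm, the Mann-Whitney-Wilcoxon two-sample rank sum test will be used for each Arm pair". The estimate is fixed too: "treatment effect for each Arm pair comparison will be expressed using the Hodges-Lehmann estimator with the 95% confidence intervals and significance levels". The variables are named as levels and scores. No baseline covariate, stratification or change from baseline is mentioned. Baseline variables are only to be summarised as mean and SD, and CO is not among those named.

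Under Baseline evaluation, "all participants will undergo a pre-treatment baseline evaluation during week 1 (run-in period"). The itemised list there includes "resting heart rate and end-expiratory carbon monoxide level (CO) through the use of a hand-held Smoklyzer" and cigarettes per day, but neither MNWS nor SCL. Those two first appear under Outcome measures: "During the active intervention period (week 2 to week 7), the following will be assessed weekly", followed by cigarettes per day, CO, MNWS and SCL. The acupressure sections start the intervention in week 2.

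On size: "A convenience sample size of a total of 60 participants will be recruited, with 20 participants per arm after randomisation". The Background gives the pilot's aim as calculating sample and effect size for future trials.

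**The concern.** The small sample is the stated reason for the rank-sum test. It may justify ranks, but it is no reason to leave a baseline measurement out. Rank ANCOVA keeps the nonparametric approach and uses the baseline as well.

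With 20 per arm, chance differences between arms at baseline are not rare. Part of any such difference carries over to follow-up and adds noise to the estimated effect. In a pilot the estimate is the main product, so this noise passes into the planning of the next trial. For CO the remedy lies in the analysis alone. For MNWS and SCL it needs a pre-treatment score, which cannot be recovered once treatment has begun.

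**Working it through.** **The plan's own figure.** 3 arms × 20 = 60, which agrees. It is a convenience sample, so there is no power calculation to reproduce.

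**Assumptions not in the document.** Two-sided alpha 0.05, 80% power for the detectable difference, a true difference of 0.8 SD, normal data, and rho (correlation of baseline with follow-up) from 0 to 0.7.

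**Chance imbalance.** The SD of a difference between two baseline means is √(2/20) = 0.316 SD. A gap above 0.5 SD in a given pair of arms therefore has probability 2 × (1 − Φ(0.5/0.316)) ≈ 0.11. On average only rho times the gap reaches the outcome, for example 0.5 × 0.5 = 0.25 SD at rho 0.5.

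**Variance and equivalent size.** Adjustment multiplies the variance by 1 − rho². The equivalent number per arm is 20/(1 − rho²). The detectable difference is (1.96 + 0.84) × √(2(1 − rho²)/20). For the unadjusted rank-sum test, 20 is replaced by 20 × 3/π, which gives 0.91 SD.

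| rho | 1 − rho² | Equivalent n per arm | Detectable difference, ANCOVA |
|---|---|---|---|
| 0 | 1.00 | 20.0 | 0.89 SD |
| 0.3 | 0.91 | 22.0 | 0.85 SD |
| 0.5 | 0.75 | 26.7 | 0.77 SD |
| 0.7 | 0.51 | 39.2 | 0.63 SD |

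**Simulated power at 0.8 SD** (20 against 20, 4,000 runs per setting):

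| rho | Rank-sum | Rank ANCOVA | ANCOVA |
|---|---|---|---|
| 0 | 0.67 | 0.66 | 0.68 |
| 0.3 | 0.68 | 0.71 | 0.74 |
| 0.5 | 0.67 | 0.77 | 0.81 |
| 0.7 | 0.67 | 0.89 | 0.93 |

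A second computation of rank ANCOVA gave 0.69, 0.78 and 0.89 at rho 0.3, 0.5 and 0.7. Under the null all three methods stayed near 0.05, so the planned test is valid.

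**CO needs a different model.** A normal shift fits CO poorly, because those who quit fall to low values largely regardless of baseline. In an illustrative mixture the assumed quit rates were 45 to 60% against 5 to 20%, with correlation 0.5 to 0.7 among continuing smokers only. The overall Spearman correlation was then only 0.16 to 0.36. Rank ANCOVA gained about 1 to 6 percentage points over rank-sum; a second mixture calculation gave about 2 to 7.

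**The case against.** **An article may leave covariate adjustment to the analysis plan.** That is true of silence, but this section names the test, the estimator and the variables. The rank-sum test could be run on changes from baseline, but the text names levels and scores. Change scores would also help little: their variance factor is 2(1 − rho), which is 1.4 at rho 0.3, 1.0 at 0.5 and 0.6 at 0.7, always above 1 − rho².

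**A pre-treatment MNWS or SCL may exist.** This stands. The flow chart is not shown, and a week-2 score could be taken before the first plaster. A reader might infer that these scales have no pre-treatment measurement at all. The document supports only that the text lists none.

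**The comparison is not confounded.** This stands. A reader might infer that a prior difference in stress or withdrawal would pass for a treatment effect. Allocation is random, so any such difference is chance and is already reflected in the confidence interval.

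**The gain may be small.** This stands in large part. A reader might take the ANCOVA powers of 0.81 and 0.93 as the expected benefit. They rest on rho of 0.5 and 0.7, which nothing in the document supports, and on normal data. A week-1 MNWS is taken while participants still smoke, so how well it predicts later withdrawal is unknown.

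**The pilot has no power target.** This is correct; power serves here only as a scale for precision. Precision matters because estimating the effect size is a stated aim.

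**Conclusion.** The planned comparison is valid but less precise than it could be at almost no cost. The loss is nil at rho 0. Under a normal shift of 0.8 SD, rank ANCOVA would gain roughly 2 to 3 percentage points of power at rho 0.3, about 10 at rho 0.5 and about 22 at rho 0.7, against about 0.67 to 0.68 for the rank-sum test. For CO a few percentage points is the realistic expectation. For MNWS and SCL the gain cannot be placed within the range, because the document gives no correlation.

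The point is confined to CO, MNWS and SCL in weeks 2 to 7. It does not touch the abstinence outcomes (PAR and CAR), nor weeks 13 and 26, when only successful quitters are assessed. It is a worthwhile improvement of modest and assumption-dependent size, not an error that invalidates the analysis.

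**What to change.** 1. For weeks 2 to 7, analyse CO for each arm pair by rank ANCOVA on its week-1 value, or by ANCOVA on log CO. The second also gives an adjusted effect with a confidence interval, which suits the pilot's aim; fix in advance how zero readings are handled.
2. Add MNWS and SCL to the existing week-1 run-in visit and adjust for them in the same way. Alternatively, state that the first week-2 score is taken before the first plaster; that score is then the baseline and not an outcome.
3. Keep the unadjusted rank-sum test with the Hodges-Lehmann estimate as a sensitivity analysis.
4. Report the observed correlation between baseline and follow-up, since the next trial's sample size can use it.

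The cost is a few sentences of analysis text, slightly more analysis, and two short questionnaires at a visit already planned. The questionnaires have to be added before participants pass the run-in.

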### Auricular acupressure versus needle auricular acupuncture

In the literature, there are two types of auricular acupuncture: with needle inserted into the acupoints or with pressure exerted at the acupoints via plastered beads. Needle auricular acupuncture involves skin penetration and carries the usual risks for acupuncture, i.e., hematoma and infection which may lead to otitis externa[31], auricular chondritis and ear deformity[32] or even subacute bacterial endocarditis[33]. Auricular acupressure via plastered beads is relatively non-invasive and can be self-administered by the recipient at times required. According to the published literature, auricular acupressure has comparable efficacy versus needle auricular acupuncture[30].

To date smoking cessation studies using auricular pressure have been sparse with conflicting results, from no better than sham[34,35] to clinically significant [26,36]. However in those studies, the number and choice of auricular points were not standardised and different types of sham treatments were used. Moreover, the outcome measures (i.e., definition of successful abstinence) were not uniform. In view of this, we design our randomised controlled pilot study to test the hypothesis that self-administered auricular acupressure is a safe and feasible method for smoking cessation, with the aim to calculate the sample and effect size for future randomised double-blind placebo controlled trials.

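### The planned effect measure (medians and the Hodges-Lehmann shift) is uninformative for the two yes/no abstinence outcomes, PAR and CAR, and no measure for proportions is named

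*Protocol article*

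**What the plan says.** Under Outcome measures, PAR and CAR head the list of five primary outcomes: "The primary outcome measures in our study will be 7-day point prevalent abstinence rate (PAR), continuous abstinence rate (CAR", followed by exhaled CO, the withdrawal scale (MNWS) and the stress checklist (SCL). Both abstinence outcomes are defined as states that a participant is or is not in: "PAR is defined as abstinence from tobacco smoking for the previous 7 days, whereas CAR is defined as abstinence since the target quit date".

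Under Statistical analysis, one method covers all five. The section speaks of "comparing the outcomes (PAR, CAR, CO levels, MNWS score and SCL scores) between Arm 1 and Arm 3" and the other two arm pairs, and then says "the Mann-Whitney-Wilcoxon two-sample rank sum test will be used for each Arm pair". Medians with quartiles and the Mann-Whitney U are to be reported. The effect measure is fixed in the last sentence: after a short qualifier limiting it to where this is possible, "treatment effect for each Arm pair comparison will be expressed using the Hodges-Lehmann estimator with the 95% confidence intervals and significance levels". No proportion, risk difference, risk ratio or odds ratio is mentioned.

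On size: "A convenience sample size of a total of 60 participants will be recruited, with 20 participants per arm after randomisation". On purpose, the Background section comparing acupressure with needle acupuncture says that the pilot is designed "with the aim to calculate the sample and effect size for future randomised double-blind placebo controlled trials".

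**The concern.** A participant's PAR or CAR at a visit is 0 or 1. The Hodges-Lehmann estimate is the median of all between-arm pairwise differences, and with 0/1 data each difference can only be -1, 0 or 1. The estimate therefore cannot vary smoothly with the quit rates. It stays at 0 until half of all pairs favour one arm, and then goes to the extreme. Medians and quartiles of 0/1 data have the same weakness: an arm with fewer than 10 of 20 abstinent has median 0, whether 1 or 9 have quit.

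At stake is the usefulness of the pilot's report. A later cessation trial is sized on quit proportions and their difference. If the analysis is done as written, the two abstinence outcomes would often show an effect of 0 when the arms differ clearly, possibly beside a small p-value.

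**Working it through.** **Inputs.** n = 20 per arm (Sample size calculation and randomisation). Quit rates come from the article: 6-20% for nicotine replacement and 30-50% for newer oral drugs (Methods of smoking cessation), approaching 45% for acupuncture (Auricular acupuncture and smoking cessation), and at most 50% for pharmacotherapy (Abstract). The 10% comparator is my choice inside the 6-20% range. The article gives no power calculation for its 60 participants, so there is none to reproduce; 3 x 20 = 60 is consistent.

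**Step 1: when the estimate leaves 0.** With a of 20 abstinent in one arm and b of 20 in the other, there are 20 x 20 = 400 pairwise differences. The number equal to +1 is a(20 - b) and the number equal to -1 is (20 - a)b; the rest are 0. The median is 0 if both counts are below 200, 1 if a(20 - b) exceeds 200, and 0.5 if it equals 200.

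- 9/20 v 2/20: 9 x 18 = 162 and 11 x 2 = 22, so the estimate is 0.
- 10/20 v 1/20: 10 x 19 = 190, so the estimate is 0.
- 11/20 v 1/20: 11 x 19 = 209, so the estimate is 1.

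The last two results differ by one quitter. Their risk differences are 45 and 50 points.

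**Step 2: how often it is 0.** I enumerated all 21 x 21 = 441 possible results and weighted them by exact binomial probabilities.

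| True rates | Probability that the estimate is 0 |
|---|---|
| 20% v 6% | 99.9% |
| 30% v 10% | 98.7% |
| 45% v 20% | 91.9% |
| 45% v 10% | 81.5% |
| 50% v 10% | 68.4% |
| 50% v 6% | 59.5% |

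If both arms end at or below 10/20, the estimate is 0 in 119 of the 121 possible results. The exceptions are 10/20 v 0/20 and its mirror image, where it is 0.5.

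**Step 3: what the reader would see, against the risk difference.** Intervals for Hodges-Lehmann use the usual Wilcoxon order statistics; those for the risk difference are Newcombe's.

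| Result | Hodges-Lehmann (95% CI) | Risk difference (95% CI) |
|---|---|---|
| 6/20 v 2/20 | 0 (0 to 0) | 0.20 (-0.05 to 0.43) |
| 9/20 v 2/20 | 0 (0 to 1) | 0.35 (0.07 to 0.57) |
| 10/20 v 1/20 | 0 (0 to 1) | 0.45 (0.18 to 0.66) |

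**Step 4: the planned test at 9/20 v 2/20.** U = 200 + (9 - 2) x 20/2 = 270, with null mean 200. With 11 ones and 29 zeros, the tie term is (1,320 + 24,360)/(40 x 39) = 16.46, so the variance is (400/12)(41 - 16.46) = 818 and z = 70/28.6 = 2.45. This gives p = 0.014 without continuity correction. A p-value of 0.014 would thus stand beside an estimated effect of 0.

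**Step 5: what U contains.** For 0/1 data, 2U/(mn) - 1 equals the risk difference, where m and n are the two arm sizes. Here 540/400 - 1 = 0.35.

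**Step 6: is the test itself at fault?** By exact enumeration at 45% v 10% and two-sided 5%, the tie-corrected rank-sum test has 74% power and Fisher's exact test 62%. With 10% in both arms, the type I error is 3.9% and 1.2%. The planned test is usable; the weakness lies in the effect measure.

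**The case against.** The strongest reply is that nothing is lost. Abstinence counts will be collected, and the U that the section plans to report converts exactly to the risk difference. That stands. A reader might infer that the pilot cannot deliver an effect size for abstinence, and the documents do not support that. But neither the conversion nor an interval for it is planned.

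Second, the qualifier before the Hodges-Lehmann sentence may be meant to exclude outcomes for which the estimator is not meaningful. That is a fair reading, and it softens the point. It does not cure it: the estimator can always be computed on 0/1 data, and if PAR and CAR are excluded the section leaves them with no effect measure.

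Third, the problem covers two of five primary outcomes. Hodges-Lehmann is a legitimate measure for CO, MNWS and SCL, and the study aim puts safety and feasibility first. That also stands.

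Fourth, a reader might infer that the estimate is 0 for practically every plausible result. At the top of the quoted range that is too strong: at 50% v 6% it is non-zero in about 40% of trials.

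Finally, a reader might infer a loss of power from heavy ties. That would need ties to go uncorrected, which the article does not say.

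**Conclusion.** The point holds as a fault in the specified summary for PAR and CAR. For these two outcomes, medians and the Hodges-Lehmann shift are largely uninformative: the shift is 0 with probability 60% to 99.9% across the quit rates examined, and otherwise almost always goes to its extreme. This undercuts the stated aim of calculating an effect size for later trials, as far as abstinence is concerned. It does not make the data inadequate, invalidate the rank-sum test, or affect the other three primary outcomes.

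The figures assume 20 analysed participants per arm, PAR and CAR analysed as one yes/no value per participant at a given visit, and true quit rates within the ranges the article quotes. Those ranges refer to varying lengths of abstinence, so they show plausible scenarios and do not forecast this trial's results.

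**What to change.** Add one or two sentences to the Statistical analysis section. For PAR and CAR, at each visit where they are assessed for all arms, report abstinent/total per arm and the risk difference with a Newcombe 95% confidence interval for each of the three arm pairs. State that this interval, and not only the point estimate, will be used in planning the next trial. Restrict medians, quartiles and the Hodges-Lehmann estimator to CO, MNWS and SCL.

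The rank-sum test may stay for PAR and CAR if the tie-corrected form is named. Replacing it with Fisher's exact test is not needed and would lower power (62% against 74% at 45% v 10%).

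The cost is analysis wording only: no extra data, visits or participants. The change should be made before the data are analysed.

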### Adverse events and withdrawal from studies

Part of the objectives of our pilot study is to assess the possible adverse effects due either to the auricular acupressure or, due to withdrawal and stress from smoking cessation. The nature and severity of the adverse effects will be recorded and assessed with the MNWS and SCL scores. At any time, participants may withdraw from the study if they develop severe nicotine withdrawal reactions or anxiety symptoms; if they have any adverse effects of pain, discomfort, inflammation or infection at the local sites of the plaster; if there is any inter-current illness that would, in the judgment of the investigators, affect outcome measures to a significant degree; and finally, as requested by the participants.

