**Discussion:**

We incorporate validated outcome measures of smoking cessation into our randomised controlled trial design with the objectives to evaluate the feasibility and possible benefits of self-administered auricular acupressure as a non-invasive alternative to pharmacotherapy for smoking cessation.

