## Methods/design

### Study aim

To demonstrate that self-administered acupressure at verum auricular acupoints is a safe and feasible option for smoking cessation, and when administered at verum acupoints whether it has benefits as compared to acupressure on non-acupoints and that without acupressure.

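### The pilot aims to show that acupressure is safe and feasible, but no listed outcome measures feasibility, and the scales named for adverse effects cannot grade plaster-site reactions

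*Protocol article*

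**What the plan says.** **Objectives.** The Background (section on auricular acupressure versus needle acupuncture) says the pilot will "test the hypothesis that self-administered auricular acupressure is a safe and feasible method for smoking cessation". The Study aim section repeats this: "To demonstrate that self-administered acupressure at verum auricular acupoints is a safe and feasible option for smoking cessation". The abstract's Discussion gives the objective as to "evaluate the feasibility and possible benefits of self-administered auricular acupressure". Two further aims are stated. The Study aim also asks about benefit over sham points and over no acupressure, and the Background wants effect and sample sizes for later trials.

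**Outcomes.** The list in Outcome measures opens with "The primary outcome measures in our study will be 7-day point prevalent abstinence rate (PAR), continuous abstinence rate (CAR" and continues with end-expiratory CO, the Minnesota Nicotine Withdrawal Scale (MNWS) and the Stress Check List (SCL). Cigarettes per day are counted. In addition, "The time taken (T) to reach the quit date is also recorded", and "expectancy of treatment will be assessed in all participants with a modified 4-item Borkovec and Nau self-assessment credibility scale". Statistical analysis compares PAR, CAR, CO, MNWS and SCL between pairs of arms and names no other outcome.

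**Adverse effects.** The section on adverse events and withdrawal sets out to "assess the possible adverse effects due either to the auricular acupressure or, due to withdrawal and stress from smoking cessation". It then says: "The nature and severity of the adverse effects will be recorded and assessed with the MNWS and SCL scores". Local reactions at the plaster site appear there only among the reasons for leaving the study. The abstract's Methods adds a weekly review of adverse effects, of which withdrawal reactions and stress are given as examples.

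**The concern.** A pilot is useful for the questions its outcomes are built to answer. Here two of the stated questions, feasibility and the safety of the plasters, are not carried through to the outcome list or the analysis.

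For feasibility, followed as written, the trial ends with no planned result: no outcome and no criterion for what would count as feasible.

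For safety, the article itself separates harm from the acupressure from harm due to quitting, then names for both a pair of scales that suits only the second. The harm specific to the intervention, a reaction under the plaster, would have no severity score. The scores that are collected may also rise or fall with how many people stop smoking, so a difference between arms in MNWS or SCL could reflect quitting rather than plasters. The planners of the later trials would then lack the tolerability and adherence figures that a pilot should give them.

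**Working it through.** The article gives no power calculation or safety margin to reproduce. Its only sample-size figure is a convenience sample of 60 in three arms of 20, and 3 × 20 = 60 agrees. The check is therefore a match of objectives to outcomes, followed by a short calculation on what 20 per arm can show.

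**Step 1: objectives against outcomes.**

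| Stated objective | Outcome or instrument named | Match |
|---|---|---|
| Feasible | None of PAR, CAR, CO, MNWS, SCL | No (0 of 5) |
| Safe: withdrawal and stress from quitting | MNWS, SCL | Yes |
| Safe: effects of the acupressure itself | MNWS, SCL | No; 0 of 5 captures local plaster effects |
| Benefit over sham and no acupressure; effect size | PAR, CAR, CO, with Hodges-Lehmann estimates where possible | Yes |

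The extra recorded items do not fill the first row. Time to quit date and cigarettes per day concern efficacy. The credibility scale touches acceptability, but it is presented as a measure of expectancy and is also given to Arm 3, which has no plasters.

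**Step 2: instruments against harms.** Outcome measures describes MNWS as a measure of nicotine withdrawal symptoms and SCL as a measure of stress. The adverse events section lists pain, discomfort, inflammation and infection at the plaster site. By the article's own description, neither scale grades these.

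**Step 3: what the sample can show.** With zero events in n participants, the two-sided 95% Clopper-Pearson upper limit is 1 − 0.025^(1/n).

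- n = 20 (one arm): 1 − 0.025^(1/20) = 0.168, or 16.8%.
- n = 40 (both plaster arms): 1 − 0.025^(1/40) = 0.088, or 8.8%.

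The chance of seeing at least one event at true rate p is 1 − (1 − p)^n. The rates are assumptions, since the article gives none:

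| p | n = 20 | n = 40 |
|---|---|---|
| 1% | 18% | 33% |
| 2% | 33% | 55% |
| 5% | 64% | 87% |
| 10% | 88% | 99% |

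Feasibility rates would be estimated somewhat better over all 60. An assumed observed rate of 80% (48 of 60) has an exact 95% CI of 68% to 89%.

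Step 3 bears only on the word *demonstrate*. The mismatch in Steps 1 and 2 would exist at any sample size.

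**The case against.** The strongest reply has three parts.

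- **Safety is not left blank.** The abstract reviews adverse effects weekly and gives withdrawal and stress only as examples. The adverse events section says the nature of adverse effects will be recorded. Departures for plaster-site reactions could be counted by arm. MNWS and SCL do fit the withdrawal and stress half of the safety objective. All of this stands. A reader might infer that the safety question cannot be answered at all; the article does not support that.
- **The efficacy outcomes are not misplaced.** Benefit over the control arms and an effect size for later trials are stated aims, and PAR, CAR and CO serve them. This also stands. A reader might infer that the design is really an underpowered efficacy trial whose primary outcomes should be replaced. The article calls the study a pilot with a convenience sample and states those aims openly, so that inference fails too.
- **A journal article leaves detail to other documents.** Grading forms and adverse-event tables are commonly kept elsewhere, and their absence alone would be no finding. This part stands only for such detail. The article does state its hypothesis, primary outcomes, analysed outcomes and adverse-effect instruments, and these do not match one another. A fuller document could add to them, but the stated mismatch would still need correcting.

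**Conclusion.** The point holds as a mismatch between stated objectives and stated outcomes, and should be corrected. None of the five primary and analysed outcomes measures feasibility, so the feasible half of the hypothesis has no planned result. For safety the gap is narrower: plaster-specific harm has no fitting severity measure and no stated comparison by arm, while a descriptive account of adverse effects remains possible.

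A secondary point concerns wording. With upper limits of 16.8% (n = 20) and 8.8% (n = 40) even when no event is seen, the trial can estimate safety but not demonstrate it. These limits assume complete data on all 20 or 40 participants and a simple yes/no event per participant. Pooling to 40 assumes that the verum and sham plasters carry the same local risk, which is reasonable because the plasters are identical and only the points differ.

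That MNWS and SCL may move with quitting rests on the article's own attribution of withdrawal and stress to cessation. Its size cannot be judged from the document.

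**What to change.** **Adverse events section.** Reserve MNWS and SCL for withdrawal and stress. Record and grade plaster-site pain, discomfort, inflammation and infection separately at each existing weekly review. Report participants affected per arm, and for both plaster arms together, with exact 95% confidence intervals. The reasons for leaving the study are not touched.

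**Outcome measures section.** Add feasibility outcomes beside the efficacy outcomes, not in place of them:

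- share of screened people who are randomised;
- weekly attendance, and retention to week 7, in all three arms;
- plaster detachments and replacements in Arms 1 and 2;
- pressing in Arms 1 and 2, from one added line in the smoking log, which the article does not say records it now.

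Give each a confidence interval and a criterion set by the investigators in advance. Week 26 retention should not be used: Outcome measures has only successful quitters assessed at weeks 13 and 26, so it would be undefined for everyone else and mixed up with efficacy.

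**Study aim.** Replace *demonstrate* with *estimate*, and align the Background sentence on the hypothesis.

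**Cost.** A short weekly item set, one log line, a small descriptive analysis and some rewording. No extra visits or participants are needed, since the screening visit, weekly reviews, smoking log and returns for detached plasters are already planned.
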